### Methods: data collection, management, and analysis

#### Data collection

To enhance data quality, measurements will be conducted twice during each session, and the modified questionnaires will undergo evaluation for their suitability among adults with presbyopia in terms of reliability and validity. This assessment will take place during the phase one of the study. In order to enhance participant retention and ensure successful follow-up, we will establish communication with the participants and provide encouragement to continue with the prescribed exercises. Moreover, in home vision therapy group, the patients are provided with a form to record the duration of their home exercises.

The optometrist responsible for recruitment in this study, [name] will conduct all the assessments. Throughout the study, [name] will maintain blindness regarding the group to which the subject has been assigned.

Table 1 displays the potential values and demographic variables of the subjects. The following variables will be recorded at the start of treatment: age, gender, distance best corrected visual acuity, near best corrected visual acuity, dry refraction, cycloplegic refraction, presence of dry eye, inter-pupillary distance and medications that may affect accommodation and vergence.

**Table 1 Tab1:** Potential values and demographic variables

Variable	Values
Age	Years
Gender	Male/Female
Distance best corrected visual acuity	Log MAR
Near best corrected visual acuity	Log MAR
Dry refraction	Diopter
Cycloplegic refraction	Diopter
Dry eye	Yes/No
Medication	Yes/No
Inter-pupillary distance	Millimeter

MAR: minimum angle of resolution

Table 2 displays the measuring tool used, assessment time, and outcome variables. A single experienced optometrist ([name]), who is also responsible for recruitment, will conduct all assessments. The optometrist conducting the assessment will be blinded to the group assigned to each participant.

**Table 2 Tab2:** outcome variables

Outcome variables	Assessment time			Measuring tool
	Baseline	1 month post treatment	2 month post treatment	
Convergence insufficiency	*	*	*	CITT definition [17]
Vergence facility	*	*	*	Prism flipper
Distance heterophoria	*	*	*	Prism cover test
Near heterophoria	*	*	*	Prism cover test
Stereopsis	*	*	*	TNO test
Prism adaptation	*	*	*	Prism trial lens
Near positive fusional vergence (blur point)	*	*	*	Prism bar
Near positive fusional vergence (break point)	*	*	*	Prism bar
Near positive fusional vergence (recovery point)	*	*	*	Prism bar
Near negative fusional vergence (blur point)	*	*	*	Prism bar
Near negative fusional vergence (break point)	*	*	*	Prism bar
Near negative fusional vergence (recovery point)	*	*	*	Prism bar
Convergence insufficiency symptom survey score	*	*	*	Questionnaire
Near point of convergence with red green lenses (break)	*	*	*	Red-Green lenses and 500 mm ruler
Near point of convergence with red green lenses (recovery)	*	*	*	Red-Green lenses and 500 mm ruler
Near point of convergence with accommodative target (break)	*	*	*	Accommodative target and 500 mm ruler
Near point of convergence with accommodative target (recovery)	*	*	*	Accommodative target and 500 mm ruler

CITT: Convergence Insufficiency Treatment Trial

Vergence facility will be assessed using a flipper prism (3 base in and 12 base out), with the target set at two lines above the best near-corrected visual acuity (20/30). The test will be conducted with the patients near glasses on and recorded at a distance of 40 cm. The distance heterophoria will be assessed by means of prism bar and alternate cover test with the digital Snellen chart set at 20/30 raw with a single letter at a distance of 6 m. The near heterophoria will be assessed by means of prism bar and alternate cover test and over the patients near glasses with a 20/30 single optotype set at 40 cm. Stereopsis will be evaluated using the TNO test with red-green filters and the patients near glasses at 40 cm. Near negative fusional vergence, with a rate of 2 prisms per second, will be obtained using prism bar and a 20/30 single E chart set at 40 cm over patients near correction (in the blur, break and recovery points). Prism adaptation will be checked by measuring the amount of heterophoria one hour after wearing the glasses, and the percentage change in heterophoria will be recorded as prism adaptation. Near positive fusional vergence (in the blur, break, and recovery point) will be measured using a base-out prism bar with a 20/30 column set at 40 cm and the patients near glasses with a rate of 2 prisms per second. The modified CISS questionnaire will be used to assess the frequency and type of symptoms before and after treatment. The near point of convergence will be evaluated using the red-green filters and accommodative target methods. A penlight will be brought close to the patient’s face, and the patient will be asked to report the diplopic image as soon as possible. This point will be recorded as the break point. The examiner will then increase the distance between the penlight and the patient’s face until a single image reappears, which will be recorded as the recovery point. The near point of convergence will be measured three times, and the results will be averaged. The near point of convergence will be recorded based on both the break and recovery points, with the patient wearing their near glasses. In the accommodative target method, participants will be guided to maintain visual singularity while a single target with a 20/30 visual acuity will be gradually brought closer to them. The movement of the target will persist until diplopia is reported or the examiner detects an objective loss of binocular vision. The target will then be moved backward until either the participant subjectively reports single vision or the examiner objectively observes the restoration of binocularity.

To ensure that the optometrist conducting the clinical testing remains unaware of the prism near spectacles, in follow up visits, all glasses will be examined in a separate unit by another optometrist and [name] will not investigate the new habitual spectacles.

To ensure and encourage adherence, a written log detailing the daily usage of near spectacles, including approximate durations and descriptions of home exercises, will be maintained. In addition, video calls will be conducted to monitor and promote compliance. Participants are strongly encouraged to remain engaged in the study. Individuals who have successfully finished the study will receive the spectacle prescription at no cost. In the event that a participant is unable to continue or cooperate, they will be replaced by another individual.

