## Methods/design

### Objectives of the study

The primary objective of this 3-parellel arm RCT is to assess the efficacy of home-based vision therapy and base in prism prescription in improvement of NPC and PFV, in presbyopic individuals who have CI. Three comparisons will be made: differentiation of the home vision therapy from base in prism prescription, and differentiation of home vision therapy from control group, differentiation of base in prism prescription from control group. Additionally, as secondary objectives, the study will involve a subjective evaluation of the clinical significance of any differences observed among groups and before and after of the interventions, using modified CISS questionnaire. We considered that a minimum variation of, 4 cm, 4 prism diopter, 6 prism diopter, and 6 points are necessary for clinically significant treatments for NPC, phoria, positive fusional vergence, and CISS score. In phase 1 we modified the CISS for elderly subjects. For this purpose, we added “Using your near optical correction” before each item and we assessed validity and reliability of the questionnaire using classical and modern analysis. Ten specialist experts in binocular vision were invited to evaluate the survey’s relevancy, clarity, simplicity, content validity ratio, and face validity. The modified CISS-P were completed twice by 50 presbyopic individuals with convergence insufficiency (CI) and 50 presbyopic individuals with normal binocular vision. Interclass correlation coefficient (ICC) for the instrument and each item were computed to assess test-retest reliability. Also we used the jMetrik software to conduct Rasch analysis. The CISS were adopted for presbyopic subjects and using ROC curve the best cut off point, sensitivity, specificity values were established for presbyopic subjects.

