#### Prism prescription group procedure

The prism prescription group will be given the same treatment protocol and instructions as the control group. However, near prismatic glasses will be prescribed using the Sheard’s criterion and their appropriated addition power, and the base in prism will be rounded up and evenly distributed between both eyes. Sheard’s criterion is most popular guideline for prism prescription and it demonstrates optimal effectiveness when applied to individuals with exophoric conditions [18]. They will also be instructed to perform random and aimless eye movements, of which will be done at a distance of 6 m and over a 2 cm area, as mentioned previously they will not affect the convergence and accommodation system.

In all groups, if participants have a refractive error for distance vision, they will be provided with two separate pairs of spectacles, one for near use and one for distance use. To ensure regular usage of the near spectacles (with or without prism) throughout the study, adherence will be monitored through video calls and by participants confirming their usage on an instruction form.

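### As written, follow-up NPC and PFV are taken through the near glasses, which carry base-in prism in one arm only, so both primary outcomes include a lens effect that favours prism

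*Protocol article*

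**What the plan says.** All references are to the protocol article.

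- **Test condition (Data collection).** For NPC: "The near point of convergence will be recorded based on both the break and recovery points, with the patient wearing their near glasses". Near PFV is "measured using a base-out prism bar with a 20/30 column set at 40 cm and the patients near glasses". Near heterophoria is assessed "by means of prism bar and alternate cover test and over the patients near glasses". Vergence facility is also done with the near glasses on. Table 2 schedules all four at baseline, one month and two months.
- **What the near glasses are.** Under Prism prescription group procedure they are prismatic, set by Sheard's criterion, and "the base in prism will be rounded up and evenly distributed between both eyes". The Control group and Home vision therapy group procedures give new near glasses with the addition and mention no prism.
- **Handling at follow-up (Data collection).** To protect masking, "all glasses will be examined in a separate unit by another optometrist", and the assessor is not to look into the new spectacles. No other test correction is named, and no step subtracts the prism.
- **Role of the measures.** Outcomes makes NPC and near PFV, at break and recovery, primary; near phoria and vergence facility are secondary. Objectives of the study says that changes of 4 cm, 4 PD, 6 PD and 6 points "are necessary for clinically significant treatments for NPC, phoria, positive fusional vergence, and CISS score".
- **Aim.** The Abstract asks which treatment better improves binocular abilities and symptom scores.

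**The concern.** A base-in prism in front of the eyes reduces the convergence a near target demands; the article's own Discussion gives this as the way prism works. If the test is done through that prism, the base-out bar reads higher at break and recovery, less exophoria is measured, and the NPC target can come closer. None of this requires any change in the patient.

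Baseline is free of this effect: the study glasses come later, and a history of prism prescription is an exclusion criterion. The test lens therefore gains prism between baseline and follow-up in one arm only. Of the three planned comparisons, prism versus control and prism versus home therapy are affected, on both primary outcomes and in the same direction. Neither a larger sample nor the planned ANOVA, ANCOVA or mixed model removes an offset that coincides with the arm. The trial could report improved binocular function when part or all of the difference is the lens.

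**Working it through.** **1. The plan's own figure.** Sample size calculation uses NPC means of 17, 16 and 21.52 cm and SD 7.50. The grand mean is 54.52/3 = 18.17. The standard deviation of the three means is √[(1.17² + 2.17² + 3.35²)/3] = 2.40, so f = 2.40/7.50 = 0.320, against the stated 0.311. With f = 0.320, 90% power needs 43 per group; 43 × 1.15 gives 50 and 43/0.85 gives 51. The stated 50 is reproduced closely enough. The sample size is not at fault here. It supplies the SD and the evaluable number, 50 × 0.85 ≈ 42 per arm.

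**2. Assumptions (not in the document).** Total base-in prism P of 2, 4 or 6 PD; inter-pupillary distance (IPD) 6.2 cm; 2.7 cm from the spectacle plane to the centre of rotation; no prism adaptation. As a plausibility check on P, Sheard's rule in the form P = (2/3) × exophoria − (1/3) × base-out reserve gives 2.0 PD for 8 and 10 PD, and 6.0 PD for 12 and 6 PD. Those clinical values are illustrative.

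**3. PFV and near phoria.** With function unchanged, both shift by P, that is by 2 to 6 PD. At 4 PD the near-phoria threshold is met by the lens alone; at 6 PD the PFV threshold is.

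**4. NPC.** Hold total vergence at break constant. Demand D = 100 × IPD/(NPC + 2.7). With prism, NPC′ = 100 × IPD/(D + P) − 2.7.

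From 17 cm, D = 620/19.7 = 31.47:
- P = 2: 620/33.47 − 2.7 = 15.8 cm, shift 1.2 cm
- P = 4: 620/35.47 − 2.7 = 14.8 cm, shift 2.2 cm
- P = 6: 620/37.47 − 2.7 = 13.8 cm, shift 3.2 cm

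From 21.52 cm, D = 620/24.22 = 25.60:
- P = 2: 19.8 cm, shift 1.8 cm
- P = 4: 18.2 cm, shift 3.3 cm
- P = 6: 16.9 cm, shift 4.6 cm

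These starting points are sample-size means, not stated baselines. From 10 cm the shifts are only about 0.5, 1.0 and 1.4 cm. IPD matters little: at 17 cm and 4 PD, the shift is 2.4 cm for 5.8 cm and 2.1 cm for 6.6 cm.

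**5. Effect on the tests if no arm changes function.** For 42 per arm and a two-sided 5% comparison of two means, the chance of a significant prism-versus-control result is about Φ[δ/(SD × √(2/42)) − 1.96].
- NPC, SD 7.5, δ = 2.2 cm: 2.2/1.637 = 1.34, giving about 27% instead of 5%. The three-group F test gives about 26%.
- NPC, δ = 3.1 cm (just under the 6 PD shift from 17 cm): about 47%.
- PFV, δ = 4 PD: about 99.6%, 86% or 63% for an assumed SD of 4, 6 or 8 PD. At δ = 2 PD: about 63%, 33% or 21%.

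The two-group figures are not adjusted for multiple comparisons; the planned Tukey procedure would lower them.

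**The case against.** The strongest counter-argument is that the article never says outright that the prismatic pair is worn at follow-up testing. One procedure is written for all visits, and the rule that the assessor leaves the new spectacles alone could mean that some other correction is used. That reading is possible, but no other correction is named, and the test descriptions specify the patient's near glasses. The masking rule can equally mean only that the assessor does not inspect the lenses. At the least, the passages need reconciling.

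Second, prism adaptation. A reader might infer that the full prism power is always counted as improvement. The documents do not support that: prism adaptation is a listed outcome, so the offset is not treated as fixed. The shifts above are upper bounds. Adaptation also means that removing the prism for the test, or subtracting it afterwards, could make the prism arm look worse than it is in daily use.

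Third, performance with the prism on is a legitimate question, since prism acts while worn. That stands, but it differs from the stated aim, and on PFV it would make a comparison with exercises depend largely on the lens.

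Three further limits stand. Negative fusional vergence is described as tested over the near correction, not the near glasses, so the text does not place it clearly among the affected measures. It is tempting to say the plan contradicts its own masking; what it shows is a risk, because the assessor may not examine the spectacles but would be testing through them. Finally, the thresholds in Objectives of the study are not a decision rule in Statistical methods, and NPC reaches its 4 cm threshold in only one of the six scenarios from 17 and 21.52 cm.

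**Conclusion.** The point holds on the plain reading. The measurement condition is stated, it differs between arms after baseline, and nothing in the article removes the difference. The direction is secure: toward prism, on both primary outcomes, in two of three comparisons.

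The size is not secure. It depends on a prism power the article does not give, on the assumed eye geometry for NPC, and on how far patients adapt. For 2 to 6 PD the no-adaptation upper bounds run from well below the protocol's thresholds to at or above them. The false-positive rates illustrate this and do not predict the trial's result. The documents do not support saying that any prism effect found would be wholly an artefact, or that masking is certain to fail.

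**What to change.** Reconcile Prism prescription group procedure with the two parts of Data collection by stating which correction is worn for each test at each visit:

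- In all arms and at every visit, measure NPC, PFV, near phoria, negative fusional vergence and vergence facility through the near correction without prism, in a trial frame set up by the unmasked optometrist. These are the primary and secondary values. This also keeps the dispensed glasses away from the assessor.
- Label any value taken through the dispensed glasses as aided performance and report it separately.
- For participants already measured, record which correction was worn and label through-prism values as aided. Subtract the known prism from PFV, and add it back to measured exophoria, only as a sensitivity analysis, because adaptation makes that correction approximate.

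For new measurements the cost is protocol wording, a trial frame and set-up time; no extra participants are needed. The real cost lies in data already collected. Trial status reports 121 randomised by 3 October 2023, leaving 29 of 150. Earlier prism-arm follow-up values may exist only in aided form, and two measurement conditions may be mixed within the trial. No simple subtraction is offered for NPC, so conclusions on prism-arm NPC must be limited accordingly.

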#### Sample size calculation

To calculate the appropriate sample size for all outcome variables specially those related to primary outcomes, a two-tailed test with α = 5% and β = 10% and 90% power was conducted using the Power Analysis & Sample Size software (PASS, version 11). The selection of appropriate statistics for the sample size determination was based on three previous studies [10, 12, 13]. The sample size in each group was determined using the One-way ANOVA menu of PASS 21 software, taking into account the quantitative nature of the dependent variables and the presence of three groups. The test was conducted with a first type error (α) of 0.05 and a second type error (β) of 0.1, corresponding to a test power of 90%. The mean values of 17 cm, 16 cm, and 21.52 cm, along with a standard deviation of 7.50, were extracted for NPC, and the effect size was calculated as 0.311. Considering a 15% dropout rate, the total number of samples in each group amounted to 50, resulting in a combined total of 150 samples.

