### Sample recruitment

#### Methods: assignment of interventions (for controlled trials)

To allocate patients to the randomized treatment groups, the patients will be categorized based on their age, gender, and the severity of their CI using random blocks. We will have 3 groups: control group, prism prescription group, and home vision therapy group. To generate a list of random numbers, the website www.random.org will be utilized. Consecutive numbers generated by the website (ranging from 1 to 150) will be assigned randomly to patients in each of the group by optometrist [name], who has no prior knowledge of the random numbers list. The optometrist responsible for intervention, [name], will be the only person who has access to the random numbers list. Due to the nature of vision therapy and other training instructions provided to the subjects, this optometrist will not be blinded. So participants get assigned consecutive numbers and then the randomized assigns treatments to each number. 1 optometrist applies the treatment. The other masked optometrist makes the measurements. Consequently, the allocation concealment will be ensured because the optometrist in charge of recruitment will be unaware of the group to which the subject will be assigned.

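### Replacing participants who stop or do not cooperate selects the analysed sample on post-randomisation behaviour, and the 15% dropout allowance makes it essentially unnecessary for power

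*Protocol article*

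**What the plan says.** Four places in the protocol article bear on this.

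- **Data collection.** After describing usage logs, video calls to support compliance and free spectacles for those who finish, the paragraph ends: "In the event that a participant is unable to continue or cooperate, they will be replaced by another individual".
- **Sample size calculation.** Attrition is already budgeted for: "Considering a 15% dropout rate, the total number of samples in each group amounted to 50", which makes 150 in total.
- **Methods: assignment of interventions.** The list is described as "Consecutive numbers generated by the website (ranging from 1 to 150"), with random blocks by age, gender and severity of convergence insufficiency. Nothing is said about how a replacement receives an arm.
- **Statistical methods.** Per-protocol principles apply, and no analysis of all randomised participants is named.

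Trial status reports 121 patients randomised by 3 October 2023, with recruitment still open.

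**The concern.** Randomisation makes the arms comparable at entry. That comparability carries through to the result only if the people randomised are the people analysed. Here a participant leaves the set because of something that happens under treatment: stopping, or not cooperating. Non-cooperation is wider than loss to follow-up, since it can cover someone who skips exercises but could still be measured. The arms receive different treatments (vergence and accommodative exercises, placebo eye movements, or prism glasses with placebo eye movements), so the reasons for stopping and the kind of patient who stops can differ by arm. A substitute who fails to cooperate falls under the same rule, so each arm is refilled until it holds people who tolerate its treatment.

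The per-protocol analysis does not repair this. Per protocol alone would leave out non-adherent participants but leave a visible gap. Replacement fills the gap, so the set looks like a complete 150. If follow-up of the replaced person ends, the data needed for an as-randomised analysis are lost too. The comparisons at stake are those on the primary outcomes, near point of convergence (NPC) and positive fusional vergence.

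**Working it through.** **Inputs, all from Sample size calculation.** Two-sided α 0.05 and β 0.1, giving 90% power; one-way ANOVA with three groups; "The mean values of 17 cm, 16 cm, and 21.52 cm, along with a standard deviation of 7.50, were extracted for NPC"; "the effect size was calculated as 0.311"; 15% dropout; 50 per group.

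**1. Effect size from the stated means and SD.** The grand mean is (17 + 16 + 21.52)/3 = 18.173. The squared deviations are 1.377, 4.723 and 11.200, sum 17.300. The SD of the means is √(17.300/3) = 2.401, so f = 2.401/7.50 = 0.320. The article states 0.311. Both are carried forward.

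**2. Reproducing the 50 per group.** Power comes from the noncentral F distribution with 2 and N − 3 degrees of freedom and noncentrality N·f², where N is the total over three groups.

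| f | n per group for 90% | power | n/(1 − 0.15) | n × 1.15 |
|---|---|---|---|---|
| 0.320 | 43 | 0.906 | 50.6, so 51 | 49.5, so 50 |
| 0.311 | 45 | 0.903 | 52.9, so 53 | 51.8, so 52 |

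The stated 50 is reproduced from the means and SD. It already contains the dropout margin.

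**3. Power without replacement.** 50 × 0.85 = 42.5 completers per arm.

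| completers per arm | f = 0.320 | f = 0.311 |
|---|---|---|
| 42 | 0.899 | 0.880 |
| 43 | 0.906 | 0.888 |
| 50 (all refilled) | 0.945 | 0.932 |

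Replacement therefore buys about 4 to 5 percentage points of power beyond what the allowance secures.

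**4. Scale of refilling.** At the plan's own 15%, 0.15 × 150 = 22.5, so about 22 places, or 7 to 8 per arm. If every loss is replaced until 150 complete, about 150/0.85 = 176.5, so 177 people, would have to enter.

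**5. Illustration of bias (assumed figures, not from the article).** Suppose cooperators gain 5 cm over control on NPC and non-cooperators gain 0 to 2 cm. With a fraction d not cooperating, the effect in all randomised participants is (1 − d) × 5 + d × g, where g is the gain in non-cooperators.

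| d | g = 0 cm | g = 2 cm |
|---|---|---|
| 5% | 4.75 | 4.85 |
| 15% | 4.25 | 4.55 |
| 25% | 3.75 | 4.25 |

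A set made up of cooperators would show 5 cm throughout, an excess of 0.15 to 1.25 cm. Objectives of the study takes 4 cm as the clinically significant change in NPC, and one of these six cells falls below it.

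**The case against.** **Replacements might still be randomised.** A reader might infer that, with 150 numbers for 150 places, a substitute must inherit a vacated number and its arm, so that randomisation is broken for each replaced slot. The article does not say this. A fresh random number is equally possible, and a condensed article may leave the mechanics to the full protocol. This stands as a limit. If a number is inherited, the person is placed by vacancy and not by chance; if not, that part falls away. Either way the original participant has left the set because of behaviour after randomisation.

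**The bias overlaps with the per-protocol analysis.** Largely the same people would be excluded under Statistical methods anyway, so deleting the replacement sentence alone would mainly lower the number analysed. This is fair. The rule compounds the per-protocol problem, and the two need one joint remedy.

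**Unequal burden is not shown.** A reader might infer that the therapy arm is hardest to complete and is refilled most. All three arms do home exercises, and the frequency and duration of the placebo exercises are not given. The documents support only that cooperation can differ by arm.

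**Dropout and compliance data are not shown to vanish.** Forms, logs and video calls are planned, and nothing says that a replaced person's records are discarded. Rates could be reported over everyone enrolled. What is missing is any statement that these people stay in the analysis.

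**Power falls slightly short at the stated f.** At 0.311, 42 to 43 completers give 88–89%, just under the planned 90%. That is correct, so replacement is essentially, not strictly, unnecessary for power.

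**Conclusion.** The point holds as a wrong rule, not as a missing detail. Followed as written, it replaces people already under treatment because they stop or do not cooperate. With only a per-protocol analysis named, the comparison on the primary outcomes is then made in a sample selected on cooperation.

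At the plan's 15% loss, about 22 of 150 places are affected. The sample size already covers that loss to within about two percentage points of the planned power. The overlap with the dropout allowance does no harm to power in itself; the harm is the selection.

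The conclusion assumes that the rule applies after randomisation, which its place among the adherence measures supports. The number of replacements made so far is unknown. The size and direction of any bias in centimetres cannot be derived from the article, and the figures in step 5 are illustrative only.

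**What to change.** - Delete the replacement sentence from Data collection.
- Keep every randomised participant in the assigned arm for the primary analysis, and move per protocol to a sensitivity analysis. Without this second step the deletion achieves little.
- Invite participants who stop treatment to the one-month and two-month measurements.
- For replacements already made, report the number per arm and how each was allocated. Keep the original participants in the analysis set with whatever data exist, and analyse with and without the replacements.

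The cost is mostly wording, plus the effort of following people who have stopped treatment. If the assumed 15% is lost, there will be about 42 to 43 complete cases per arm instead of 50, with the power shown in step 3. With 121 patients already randomised at the reported date, missed visits of anyone already replaced may be unrecoverable, and the report should say so.
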